## BACK GROUND

Diabetes Mellitus (DM) is a chronic metabolic disorder characterized by hyperglycaemia with or without glycosuria, resulting from absolute or relative deficiency of insulin, its action or both[1]. Latest studies show, Diabetes is the fastest growing health emergencies of the 21st century. 'Pre-Diabetes' is a term increasingly used for people with impaired glucose tolerance and/or impaired fasting glucose. It signifies a risk of future development of type 2 DM and Diabetes-related complications [2]. According to the International Diabetes Federation, India is one among the epicentre of DM and it was found that in 2000, the global estimate of adults living with Diabetes was 151 million. Also, IDF estimates that there will be 578 million adults with Diabetes by 2030, and 700 million by 2045[3, 4]. In course of time, individuals with Diabetes are more susceptible to develop any associated complications of kidneys, heart, blood vessels, nerves and eyes. As the number of diabetic patients has been increasing in India, diabetic complications are the most important target to be prevented.

## RATIONALE

Indian Council of Medical Research initiated a multicenter study on DM on 1971. The prevalence of the disease was found to be 2.1% in the urban areas and 1.5% in the rural areas in six cities and surrounding villages in India including Ahmadabad, Kolkata, Cuttack, Delhi, Pune and Trivandrum [5]. Prevalence of Diabetes in India study, evaluated the prevalence of Diabetes mellitus in small towns and villages of India, which was found to be 5.9% and 2.7%, respectively [6].

Once Diabetes is established, it tends to be lifelong. Prognosis depends largely on the presence or absence of chronic vascular complications. Present day treatment has served to prevent or successfully overcome acute complications like ketoacidosis, infections, hypoglycaemia and lactic acidosis. There are long term complications affecting the heart, kidneys, eyes, nerves and blood vessels. These complications can be prevented to a great extent by rigid diet control, exercise and regular therapy. Once established the degenerative complications progress relentlessly and lead to damage of vital organs like the kidneys, heart and brain unless properly managed [7]. For people living with Diabetes, access to affordable treatment, including insulin, is critical to their survival. There is a globally agreed target to halt the rise in Diabetes and obesity by 2025[8].

## JUSTIFICATION FOR CONDUCTING THE TRIAL

The Dietary Supplement Health and Education Act (DSHEA) of 1994 define a dietary supplement as a “product taken by mouth that contains a dietary ingredient intended to supplement the diet.” These dietary ingredients may consist of “vitamins, minerals, herbs, amino acids, and other botanicals and substances such as enzymes, organ tissues, glandulars, and metabolites” [9]. According to the 2017 Standards of Medical Care in Diabetes, “Each person with diabetes should be actively engaged in education, self-management, and treatment planning with his or her health care team, including the collaborative development of an individualized eating plan” [10]. Thus nutritional therapy is much essential for Pre-diabetic and Diabetic patients for providing optimum diabetes care.

Studies have shown that poor eating habits are the main factor behind the disease DM. Also, diabetic subjects usually follow unhealthy eating habits which impair daily health and wellbeing. This habit can also affect the mental health, energy levels, complexion, and overall well-being. More over it is scientifically proven that DM subjects have decreased levels of Vitamin A, C and E. To overcome this, a supplement can be used to fill in nutritional gaps of the diet. Conventional medical system had a great deal to offer in this regard. Various ingredients in DiabetEaze Powder such as Amalaki, Krishna Jeeraka, Shigru, Kalamegha, Ragi and Yava provides minerals, micro elements and amino acids which are essential for a diabetic person to overcome the oxidative stress. Also Vitamin B complex, C and E in Amalaki, Krishna Jeeraka, Shigru, Kalamegha, Ragi, Yava, Vrikkaphala and Panasa will help to overcome oxidative stress, boost the immune system and reduces the risk of development of various diabetic complications. DiabetEaze powder also ensures that person is getting a measurable amount of essential nutrients which make up for the poor nutrient content of the many foods one eats.

## STUDY OBJECTIVES

### Primary objective:

- ❖ Clinical Nutritional Assessment of DiabetEaze Powder in Type 2 DM
- ❖ To assess the variation in Quality of Life in terms of direct symptoms.
- ❖ To assess the role of DiabetEaze Powder in managing nutritional inadequacy in DM.

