|                                                           | Andrographis paniculata (Kalamegha)
Artocarpus heterophyllus (Panasa)
Eleusine coracana (Ragi)
Hordeum vulgare (Yava)
Anacardium occidentale (Vrikkaphala)
Theobroma cacao (Rasalaphala)                                                                                                                                                                                                                                                                                            |
| ROUTE OF ADMINISTRATION                            | Oral                                                                                                                                                                                                                                                                                                                                                                                                                                                                                                                                         |
| PROOF OF CONCEPT                                   | This formula of the nutritional supplement is based on traditional knowledge.                                                                                                                                                                                                                                                                                                                                                                                                                                                                |
| INVESTIGATIONAL PRODUCT, MANUFACTURING, AND DOSAGE | 
The study drug DiabetEaze is a poly herbal formulation for providing nutritional support to Pre-Diabetes & Type 2 Diabetes Mellitus. Also, it is aimed to reduce complications and to improve quality of life in Type 2 Diabetes Mellitus.
 
The study drug will be manufactured in GMP certified factory of Pankajakasthuri Herbals India Pvt. Ltd, Thiruvananthapuram, Kerala, India.
 
Dosage– 10g/day [5g twice daily]
                                                                                              |

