| EVALUATION CRITERIA                                | Clinical, Haematological and Biochemical assessments                                                                                                                                                                                                                                                                                                                                                                                                                                                                                         |
| ASSESSMENT SCHEDULE                                | 
The initial assessment will be done before the commencement of the study (0th day) and simultaneously the study will be initiated. Further assessment will be done on the 3rd month and will be followed on every six months till the completion of the study (i.e. 90th, 180th, 365th, 545th& 730th day). Interim data analysis will be done at the end of first six months (180th day) and report will be published in reputed journal.
 |
| STATISTICAL CONSIDERATION                          | Appropriate statistical analysis will be performed. p value ≤0.05 indicates that the study is statistically significant.                                                                                                                                                                                                                                                                                                                                                                                                              |
| DURATION OF STUDY                                  | The initial study period is 24 months, if required the study can be extended.                                                                                                                                                                                                                                                                                                                                                                                                                                                                |

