|                                 | 
given. Placebo for this trial will be given in the similar form as that of the trial drug. Placebo must be consumed according to the same procedures and guidelines as DiabetEaze Powder.
                                                                                                                                                                                                                                                                                                                                                                                                                                                                                                                  |
| CRITERIA FOR EVALUATION: | 
Efficacy:
 
 
• Fasting Blood Sugar
 
• Post Prandial Blood Sugar
 
• Oral Glucose Tolerance Test
 
• HbA1c
 
• Urine Sugar
 
• Investigation for Vitamins & Minerals
 
• Investigations for Diabetic Nephropathy
 
• Investigations for Diabetic Cardiopathy
 
• Investigations for Diabetic Neuropathy
 
• Investigations for Diabetic Retinopathy
 
• Other Laboratory investigations– CBC, Lipid Profile, LFT, RFT, CRP, Urine Examination etc.
 
 
Safety:
 
 
• ADR/AEs using MedDRA
 
• RFT & LFT
 
 |

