## **Informed Consent**

Fully informed consent will be obtained before any study specific procedures are performed. The content and process of obtaining informed consent must be in accordance with all applicable ethical and regulatory requirements. Informed consent form must be signed by the subject voluntarily. In a situation where a subject is unable to provide consent for him/her, informed consent will be obtained from a Legally Authorized Representative (LAR) / next of kin / legally appointed individual in person in the presence of an impartial witness.

## Screening / Randomization, Visit – Day 0

Subjects must meet the inclusion criteria and have none of the exclusion criteria in order to be eligible for randomization in this study. Subjects who meet all eligibility criteria and have signed informed consent will be included under Baseline study visit. Randomization minimizes systematic bias in the selection and assignment of patients to study therapy and provides justification for inferential statistical methods to be used on data from this study. Once the subject is randomized the sponsor representative or the study Investigator will provide the study staff with a unique randomization number for the subject.

Following assessments must be made at this Baseline visit for each study subject:

- Demographics
- Medical History (all known information regarding the subject's health history/relevant surgeries/interventions, prior to signing the informed consent).
- Vital signs: Body temperature, Pulse – beats per minute (BPM), Blood Pressure (BP) mmHg, Respiratory Rate – breaths per minute
- Concomitant medications
- General Examination -
- Systemic Examination: Examination of Respiratory, Cardiovascular, Nervous, Musculo-skeletal and Integumentary System
- BMI
- Blood will be obtained for following laboratory tests:
  - FBS
  - HBA1C
  - Urine- sugar
  - PPBS
  - OGTT
- Investigation for Vitamins & Minerals, Diabetic Nephropathy, Diabetic Cardiopathy and other investigations like CBC, Lipid Profile, RFT, LFT, CRP, Urine Examinations etc.
- Screening for Diabetic Neuropathy& Retinopathy.

## Short term assessment, Visit – Day 90

Following assessments must be made at this Baseline visit for each study subject:

- Vital signs: Body temperature, Pulse – beats per minute (BPM), Blood Pressure (BP) mmHg, Respirations – breaths per minute
- Concomitant medications
- General Examination

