#### **Interim assessment, visit – Day 180**

Following assessments must be made at this Baseline visit for each study subject:

- Vital signs: Body temperature, Pulse – beats per minute (BPM), Blood Pressure (BP) mmHg, Respirations – breaths per minute
- Concomitant medications
- General Examination
- Systemic Examination: Examination of Respiratory, Cardiovascular, Nervous, Musculo-skeletal and Integumentary System
- BMI
- Blood will be obtained for following laboratory tests:
  - FBS
  - PPBS
  - HBA1C
  - OGTT
  - Urine- sugar
- Investigation for Vitamins & Minerals, Diabetic Nephropathy, Diabetic Cardiopathy and other investigations like CBC, Lipid Profile, RFT, LFT, CRP, Urine Examinations etc.
- Screening for Diabetic Neuropathy & Retinopathy.

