#### **End of treatment/Trial visit (EOT) - Day 730**

Following assessments must be made at this EOT visit for each study subject

- Vital signs: Body temperature, Pulse – beats per minute (BPM), Blood Pressure (BP) mmHg, Respirations – breaths per minute
- Concomitant medications
- General Examination

- Systemic Examination: Examination of Respiratory, Cardiovascular, Nervous, Musculo-skeletal and Integumentary System
- BMI
- Blood will be obtained for following laboratory tests:
  - FBS
  - PPBS
  - HBA1C
  - OGTT
  - Urine- sugar
- Investigation for Vitamins & Minerals, Diabetic Nephropathy, Diabetic Cardiopathy and other investigations like CBC, Lipid Profile, RFT, LFT, CRP, Urine Examinations etc.
- Screening for Diabetic Neuropathy & Retinopathy.

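### Quality of life in terms of symptoms is a primary objective, but the protocol's visible text specifies no defined or scored measure of it in the efficacy criteria or in any itemised visit list.

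*Protocol*

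**What the plan says.** The protocol's Study Objectives section lists three primary objectives. The second is "To assess the variation in Quality of Life in terms of direct symptoms", and the Clinical Trial Summary repeats it. The Summary's entry on the investigational product says that the product is also meant "to improve quality of life in Type 2 Diabetes Mellitus".

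What is to be measured is set out in three places:

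- The Evaluation Criteria row of the Summary names only broad classes: "Clinical, Haematological and Biochemical assessments".
- The Criteria for Evaluation row has an efficacy list, which ends with other laboratory tests ("Lipid Profile, LFT, RFT, CRP, Urine Examination etc"), and a safety list made up of "ADR/AEs using MedDRA" plus renal and liver function tests.
- Itemised visit lists are given for Days 0, 90, 180 and 730. The Day 0 list opens with "Following assessments must be made at this Baseline visit for each study subject", wording that recurs at Days 90 and 180. The last opens with "Following assessments must be made at this EOT visit for each study subject".

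**The concern.** A change in quality of life needs the same measure taken before treatment and again afterwards. The protocol writes out its assessments item by item and makes them mandatory, yet the measure that this primary objective needs is not among them.

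This is not detail that can wait for a statistical analysis plan. Such a plan can say how a score is analysed, but it cannot supply a Day 0 score that nobody was told to collect. Without one, any later statement on quality of life would rest on unscored notes selected after the fact. The Day 180 interim report, which is to be published, would be the first place where this showed.

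**Working it through.** The protocol gives no figure to reproduce here. The check sets the objective against every place where measurements are specified.

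**Efficacy criteria (Clinical Trial Summary, Criteria for Evaluation).** There are 11 items:

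1. fasting glucose
2. post-prandial glucose
3. oral glucose tolerance test
4. HbA1c
5. urine sugar
6. vitamins and minerals
7. nephropathy
8. cardiopathy
9. neuropathy
10. retinopathy
11. other laboratory tests

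Quality-of-life or symptom measures: 0 of 11.

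**Visit lists.**

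| Visit | Content | Quality-of-life or symptom measure |
|---|---|---|
| Day 0 | Demographics, medical history, vital signs, concomitant medication, general and systemic examination, BMI, laboratory and complication investigations, neuropathy and retinopathy screening | None |
| Days 90, 180 and 730 | As Day 0, without demographics and medical history | None |
| Days 365 and 545 | Scheduled, but no list given | Cannot be judged |

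That is 0 of 4 itemised visits. The other 2 of the 6 scheduled visits have no stated content.

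**Could a listed item serve as the measure?** Each candidate was asked whether it is scored, whether it is available both at Day 0 and later, and whether it is linked to this objective.

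- *Systemic examination* ("Systemic Examination: Examination of Respiratory, Cardiovascular, Nervous, Musculo-skeletal and Integumentary System"). It recurs at every itemised visit, but it is a clinician's examination by organ system. No symptom scale or score is attached to it.
- *Medical history.* It is listed at Day 0 only and covers the time before consent, so no later value pairs with it.
- *Neuropathy screening.* It recurs, but it concerns one complication, and the efficacy list enters it as such.
- *Adverse events.* These are graded and dated, but the examples given are new events, increased severity of a baseline event and worsening laboratory values. Such records show deterioration. They do not measure the improvement that the product is meant to bring.
- *Clinical assessments*, as a class. This is a general label. The visit lists show what it contains, and none of that content is a symptom score.

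No candidate meets all three conditions.

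**The case against.** The strongest reply is that the objective is narrower than quality of life at large: it is limited to direct symptoms. All four itemised visits require general and multi-system examination and neuropathy screening, Day 0 adds a history, and unfavourable symptoms are recorded as adverse events with grade and dates. Some symptom information will probably exist. This stands. A reader might infer that the trial would hold no data at all on this objective, but the documents do not support that. What is missing is a defined, scored measure with a baseline.

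Second, the flow chart and milestones are figures that are not shown, and the case report form is not supplied. An instrument may be named there, so the finding covers the visible text only. Even in that case, the mandatory lists and the efficacy criteria would omit it and need correcting, because the Documentation section has the case report form record what the protocol requires.

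Third, a reader might infer that symptom notes would necessarily be read by unblinded staff. The protocol does not settle this. It calls the design open, yet it provides a placebo in similar form and, under Serious Adverse Events, refers to unblinding. No conclusion on assessor bias is drawn here.

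Finally, neither the sample size nor any stated hypothesis is tied to this objective, and the gap does not harm the glycaemic or micronutrient data. That is correct, and it limits the consequence to this one objective.

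**Conclusion.** The point holds in this form: the primary objective on quality of life cannot be answered from the assessments the protocol specifies. Its size is a count, not an effect estimate: 0 of 11 efficacy criteria and 0 of 4 itemised visit lists carry a defined or scored quality-of-life or symptom measure, and the two remaining visits have no list. One of three primary objectives is affected.

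The conclusion assumes that the unseen flow chart and case report form add no instrument, and that the visit lists are followed as written. The matter needs correcting before subjects start treatment, because a missing pre-treatment value cannot be obtained afterwards.

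**What to change.** Name one scored instrument. A validated questionnaire would serve, and so would a predefined, structured symptom score, which fits the objective's wording closely. Because the objective names no disease group, the instrument should suit both type 2 diabetes and pre-diabetes.

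- Add it to the efficacy list under Criteria for Evaluation.
- Add it to the Day 0, 90, 180 and 730 lists, and write lists for Days 365 and 545 that include it.
- Compare change from Day 0 between groups within each disease stratum: Group 2 with Group 1 in pre-diabetes, and Groups 4, 5 and 6 with Group 3 in type 2 diabetes. State the visit at which the objective is judged.

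If the sponsor does not wish to collect it, remove the quality-of-life objective from both the Summary and the Study Objectives section, together with the matching aim in the Summary's investigational product entry. Deleting the objective alone would leave that aim standing with nothing to support it.

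The cost of collecting it is a short form at each visit, extra case report form pages and possibly translation, licensing or help with completion. Removing it costs only a text amendment. Neither route changes the sample size of 180.

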### Secondary objectives:

- ❖ Assessment of hypoglycaemic effect of DiabetEaze Powder.
- ❖ Assessment of effect of DiabetEaze Powder in Pre-Diabetes.
- ❖ Assessment of reduction in complications.

## **ELIGIBILITY CRITERIA**

Subjects are eligible to be included in the study, if they meet the following criteria:

### **Main inclusion criteria**

1. Willing to sign consent form
2. Men and women aged 40 years or greater and not older than 65 yrs.
3. Subjects with clinical evidence of Type 2 DM
4. Subjects of Pre-Diabetes with HbA1c range between 5.7% and 6.4% and/or OGTT range between 140 mg/dl and 199 mg/dl.

### **Main exclusion criteria**

1. Presence of conditions like medical, psychological, social or alcohol abuse that would either interfere with participation in the trial.
2. Subjects with known allergy to any of the ingredients of the drug product.
3. Pregnant or lactating women
4. Subjects with Type1 DM.
5. Subjects undergoing insulin therapy.
6. Subjects with fluctuating blood sugar level.
7. Other conditions like CKD, malignancies etc.
8. Post-surgical cases mainly GI diseases.
9. Patients under steroid intake

## **DURATION OF THE STUDY**

The initial study period is 24 months. If required, the study can be extended.

### **STUDY PERIOD**

Begins at the first trial drug dose and ends at the trial completion. These dates are reported on the both paper based and electronic version Case Report Form (CRF/eCRF).

### **STUDY COMPLETION AND END OF THE STUDY**

This trial will be considered complete (i.e. the scientific evaluation will be complete) following the evaluation of final outcome data. Investigators will continue the study if required. The End of the trial refers to the date of last visit (Day 730) or last schedule assessment for the last subject. The end of trial occurs after the study completion and after the last subject has discontinued the trial.

